### Supplementary Sub-Study: Quality Improvement Audit of ESC Uptake

To evaluate the practice of ESC, a quality improvement exercise will be conducted to assess the utilisation of ESC before and during the proposed pilot feasibility RCT detailed above. This evaluation will employ a medical records audit methodology, which is a recognised approach for examining the delivery of clinical care and identifying areas for improvement [40]. Data will be collected using a purpose-designed checklist (Appendix D) to guide data extraction for any ESC aligned assessment and practice elements such as the DT, eRFA, and supportive care referrals, i.e., allied health and social support services.

The audit process will involve randomly selected patient records for each audit phase (before, during, and after) based on unique record numbers obtained from the reception staff. These record numbers will be assigned an Audit ID and then randomly selected using an Excel random number generator.

The sample size for the audit will depend on the specific phase being evaluated. For the baseline phase (pre-PhotoVoice optimised ESC), assuming N = 800 patient records for the calendar year 2020 and an estimated 10% ad hoc use of ESC before formal implementation (*p* = 0.1), a sample size of 118 records will be audited to achieve a 95% level of confidence (Z = 1.96) and a 5% margin of error (E = 0.05) and relative standard error (RSE) = 0.5. This is based on the desired proportion (10%) sample size formula n = (N × Z^2 × *p* × (1 − *p*))/[(N − 1) × E^2 + Z^2 × *p* × (1 − *p*)/(N × RSE^2)].

During the three months of PhotoVoice-optimised ESC as a structured implementation process, assuming 200 eligible records (a quarter of the annual throughput) and a 50% adoption of ESC, a sample size of 132 records will be randomly selected and audited to achieve a 95% level of confidence and a 5% margin of error and RSE = 0.5.

The audit data will be analysed using summary descriptive statistics, including means, standard deviations, proportions, and 95% confidence intervals. Comments from the audit checklist will be subjected to content and/or thematic analysis.

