Implementation of PhotoVoice in our study is undergirded by the Bronfenbrenner model [27]. The model is based on the theory that understanding individuals and their behaviours is underpinned by the reciprocal interaction between individuals and their environment. Its domains include the individual, microsystem (immediate relationships), mesosystem (connections between microsystems), exosystem (indirect influences), and macrosystem (broader cultural factors), representing the multidimensional nature of development and its interconnected influences [27].

The study objective is to investigate the feasibility and acceptability of implementing PhotoVoice in addition to usual care in a regional cancer centre. Usual care in this context is defined as ESC that incorporates geriatric assessment. Given the early stages of ESC, a secondary aim is to undertake a quality improvement exercise to examine aspects of ESC adoption using a medical records audit. The primary and secondary research questions are, respectively, (i) what is the feasibility, acceptability, and utility of PhotoVoice to enable empowerment, patient-centred care, and shared decision making for older adults diagnosed with a cancer in a regional cancer centre? and (ii) using a medical records audit, what is the level of uptake of supportive (non-medical) care practice as demonstrated by a range of tools as proxies for supportive care including use of the distress thermometer (DT), electronic rapid fitness assessment (eRFA) and referrals to supportive care services before and during the implementation of PhotoVoice?

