## Appendix D. Audit Checklist

Patient’s Age: ________
Gender: ☐Male ☐Female ☐Other
ATSI: ☐Yes ☐No
Diagnosis: _________________________________________________
Treatment regimen: _________________________________________

**Item**	**Yes/No**	**Comments**
G8	☐Yes ☐No	Score if yes:
DT	☐Yes ☐No	
eRFA	☐Yes ☐No	
TUG	☐Yes ☐No	
Mini-Cog	☐Yes ☐No	
Allied health referral(s)	☐Yes ☐No	
If yes for above, specify		
Other supportive care services	☐Yes ☐No	
If yes for above, specify

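### The audit's 'during' quarter is named for PhotoVoice but covers all throughput, and the checklist records no trial status or arm, so a rise in uptake, above all in referrals, cannot be apportioned between ESC roll-out and the trial

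*Protocol article*

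**What the plan says.** The Background sets the second research question as the level of uptake of supportive care, measured by the distress thermometer, the eRFA and "referrals to supportive care services before and during the implementation of PhotoVoice". The same section calls ESC itself early-stage and gives examination of its adoption as the secondary aim.

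The audit sub-study section defines the two phases that have a sample size:

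- **Baseline.** "assuming N = 800 patient records for the calendar year 2020", with "an estimated 10% ad hoc use of ESC before formal implementation"; 118 records are to be audited. The section also labels this phase as preceding PhotoVoice-optimised ESC.
- **During.** "During the three months of PhotoVoice-optimised ESC as a structured implementation process, assuming 200 eligible records", glossed as one quarter of the annual throughput, with 50% ESC adoption assumed; 132 records are drawn at random.

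The analysis is descriptive: means, standard deviations, proportions and 95% confidence intervals, with no stratification mentioned. Record numbers are recoded to an Audit ID, and no link to the trial's enrolment list is described.

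Appendix D prints the checklist: age, gender, ATSI status, diagnosis, treatment regimen, G8 (with score), DT, eRFA, TUG, Mini-Cog, allied health referrals and "Other supportive care services". It has no item for trial participation, arm or PhotoVoice.

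**The concern.** The phase label implies that the audited quarter shows care with PhotoVoice. PhotoVoice is given only to consenting patients with G8 of 14 or below who are randomised to the intervention arm (Sections 3.1 to 3.4). The audited quarter is drawn from everyone.

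Two changes separate the phases: ESC moves from ad hoc use to formal implementation, and the trial starts. For one audited outcome the trial has a direct route of influence, since Section 3.4 says that referrals to allied health and social supports may follow from the PhotoVoice and MDT discussions. If referrals rise, the audit as planned cannot say how much belongs to roll-out and how much to the trial. The answer to the second research question, which is worded around PhotoVoice, would then be hard to interpret and easy to misread.

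**Working it through.** **1. The plan's sample sizes.** The usual single-proportion formula with finite-population correction is n = N·Z²·p(1−p) / [(N−1)·E² + Z²·p(1−p)], with Z = 1.96 and E = 0.05.

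- Baseline, N = 800 and p = 0.10: Z²p(1−p) = 0.3457, so n = 276.60 / (1.9975 + 0.3457) = 118.04. The stated 118 is reproduced.
- During, N = 200 and p = 0.50: Z²p(1−p) = 0.9604, so n = 192.08 / (0.4975 + 0.9604) = 131.75. The stated 132 is reproduced.

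The formula as printed, with its extra divisor N × RSE², gives 138.4 and 371.7 instead. That is a separate matter and does not affect this point.

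**2. Who is in the 'during' frame.** Section 2.2 gives an annual intake of nearly 800 patients aged over 69, and 800 / 4 = 200. The frame is thus the full quarterly intake. Although its records are called eligible, nothing has been taken off for G8 score, consent or allocation. It contains intervention patients, controls, decliners and patients with G8 above 14.

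**3. How many audited records can be PhotoVoice records.** With 1:1 allocation and a share t of audited records from participants, the expected number is 132 × t / 2. The document gives no t, so these shares are assumed:

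| t | PhotoVoice records of 132 | Share |
|---|---|---|
| 10% | 7 | 5% |
| 30% | 20 | 15% |
| 50% | 33 | 25% |
| 100% (ceiling) | 66 | 50% |

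**4. Why the causes cannot be separated.** For any audited item, the overall proportion is U = (1−t)·a + (t/2)·c + (t/2)·v, where a, c and v are the proportions in non-participants, controls and PhotoVoice patients. The planned data give U alone. Two assumed mixtures both return the planning value of 50%:

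- t = 44.4%, participants (c and v) at 100%, others still at the 10% baseline: 0.444 + 0.556 × 0.10 = 0.50.
- t = 10%, participants at 100%, others at 44.4%: 0.10 + 0.90 × 0.444 = 0.50.

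The first means no change outside the trial; the second means substantial adoption. These values only show that U does not identify its parts. They do not predict participants' uptake.

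**5. Why non-participants versus baseline is not the answer.** All participants have G8 of 14 or below, the group due the eRFA under Section 3.5. Taking them out leaves a group with relatively more patients above 14, whereas baseline records are not filtered in this way. Assume that half of all patients score 14 or below, that all of those complete the eRFA, and that 20% of records are participants. Overall uptake is 50%, but non-participant uptake is (0.50 − 0.20) / 0.80 = 37.5%, which is 12.5 points lower with no trial effect at all.

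**The case against.** The strongest reply is that the audit makes no claim about PhotoVoice. Its stated aim is ESC uptake, the analysis is descriptive, and PhotoVoice is judged between the randomised arms (Section 3.7). On this reading, the reference to PhotoVoice in the research question only marks the period. This stands in so far as no causal claim is made. It does not explain a label that describes care most of the frame may not receive, nor does it help a reader interpret a rise in referrals.

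A second reply is that participants could be identified later by matching record numbers to the enrolment list. That is possible, and an article may omit such a step. But the checklist is printed in full without the field, and the analysis described makes no use of it.

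A stronger reading is tempting: that trial participation drives completion of the assessments and so inflates routine uptake. If participants had complete records, 30% of other patients had ESC uptake and 20% of records were participants, the audit would show 0.20 + 0.80 × 0.30 = 44%. The documents do not support this as a finding. G8 screening precedes consent (Section 3.1), and the eRFA, TUG and Mini-COG are usual care for every patient scoring 14 or below, enrolled or not (Section 3.5). All three inputs are assumptions, and the 50% adoption figure is a planning value for sample size, not a target.

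**Conclusion.** The point holds as a cheap improvement to a supplementary audit, not as a flaw in the trial. The label does not fit the frame, roll-out and trial fall between the same two phases, referrals can be generated by PhotoVoice, and the planned data contain nothing to tell these apart. A before/during rise, most clearly in referrals, cannot be apportioned between ESC roll-out and the trial.

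The firm figure is the ceiling of about 66 PhotoVoice records among 132, which rests only on 1:1 allocation. The size of any distortion is unknown, because no enrolment share is given. That participation also raises completion of the assessments is plausible but not shown. A reader might also infer that the audit sets out to prove a PhotoVoice effect; its stated aim and descriptive analysis do not support that.

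**What to change.** - Add one item to Appendix D: trial participant, with the options no / ESC arm / PhotoVoice arm.
- Keep the overall 'during' proportion as the estimate of uptake, and report it also by that item.
- Show eRFA, TUG and Mini-Cog within G8 of 14 or below where G8 is recorded. The checklist already captures the score. At baseline this subgroup may be small: if G8 recording follows the assumed 10%, about 12 of 118 records would have a score.
- Do not make non-participants versus baseline the main estimate.
- Rename the phase 'ESC roll-out with the trial running', and state that the before/during change is not evidence about PhotoVoice.

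The cost is one field, a check against the enrolment list and one table. Stratum intervals will be wider than the planned 5% margin. For example, with an assumed 20% participant share and p = 0.50, 106 of 160 non-participant records give 1.96 × √(0.25/106) × √(54/159) = 5.5 points, and 13 of 20 PhotoVoice records give 1.96 × √(0.25/13) × √(7/19) = 16.5 points. The arm-level rows are therefore descriptive only.

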## 4. Expected Results

By capturing older adult patients’ perspectives, priorities, and barriers during geriatric assessment, we anticipate that PhotoVoice will provide valuable insights into the acceptability and benefits of this novel approach. Successful integration of PhotoVoice into the ESC framework has the potential to attract interest in the geriatric assessment space by empowering healthcare providers to develop tailored management plans that align precisely with the unique needs and preferences of older adults with cancer. This approach has the capacity to bridge communication gaps, improve shared decision making, and enhance the overall care experience for the older adult population undergoing treatment for cancer. By taking cognisance of the voices and perspectives of older patients, this study could promote better outcomes and improved quality of life. The integration of PhotoVoice into ESC signifies commitment to bridging communication gaps and fostering meaningful engagement between healthcare providers and older adults diagnosed with cancer. Expanding understanding of how PhotoVoice may enhance geriatric assessment, could promote personalised care that addresses the needs and concerns of older adults, ultimately improving their treatment experiences and overall well-being during their cancer care journey. Our findings will contribute to the growing body of evidence supporting the integration of patient-centred approaches in geriatric oncology.

Finally, identifying enablers and barriers during the implementation process may lead to refining the intervention process and optimise its effectiveness. The findings will guide future advancements, ultimately informing the design of large-scale implementation and effectiveness trials. This could pave the way for broader integration of the PhotoVoice approach into geriatric assessment across diverse healthcare settings.

## 5. Conclusions

This study aims to investigate the use of PhotoVoice discussion of patient-derived photographs, a novel methodology in the context of cancer care geriatric assessment and ESC in a regional cancer care centre. The integration of PhotoVoice into the ESC framework has the potential to attract interest that fosters the development of tailored management plans that align with the unique needs and preferences of older adults diagnosed with cancer. Beyond immediate implementation considerations, this study may contribute to the broader field of geriatric oncology. The findings could potentially contribute to enhancing patient-centred care and pave the way for further research in this field, particularly in a definitive implementation and effectiveness trial of PhotoVoice.

## Figures and Tables

**Figure 1 mps-06-00068-f001:**
[figure not shown]
Summary of study design and participant flow.

## Data Availability

Not applicable.

## Appendix A. Clinician Survey

1. Please tell us about yourself:
1.1. Discipline/Specialty:

Allied health
Medical (physician, GP)
Nursing
Non-clinical supportive service

1.2. Years in practice: _________________________________
1.3. Do you have experience in cancer care: Yes/No

If yes, how many years of experience? ________

2. What did you like about the ESC initiative? ___________________________________________________________________________________________________________________________________________________________________________________________________________________________________________________________________________________________________________________________
3. What did you dislike about the ESC initiative? ____________________________________________________________________________________________________________________________________________________________________________________________________________________________________________________________________________________________________________________________
4. In thinking about the multidisciplinary team meetings:
4.1. How many meetings did you attend Between February and May 2021 (NB. date will be adjusted depending on when meetings formally start)? ____________________
4.2. Please rate the MDT meetings on the following
4.2.1. Time of the meeting

Suitable
Unsuitable
Preferred a different time (specify): _____________________

Comments:
____________________________________________________________________________________________________________________________________________________________________________________________________________________________________________________________________________________________________________________________

4.2.2. Frequency of the meeting

Too long
Too short
Just right

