### 3.6. Recruitment

After obtaining ethical approval, all patients presenting for their first appointment with any of the medical oncologists or haematologists during the period from February 2021 to January 2022 with a G8 score ≤14 would be offered enrolment in the study. The attending medical oncologist or haematologist would provide the patient with a participant information and consent document. Patients expressing interest in the study would be referred to the research team member (for a detailed study briefing), followed by obtaining informed consent. Prospective participants requiring more time to decide on participation would be given up to two business days to consider before following up if they had not responded.

All members of the MDT will receive a study briefing and invitation to participate during their weekly team meeting. They will be asked to complete a clinician survey (Appendix A), and consent will be implied by returning a completed survey.

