4.2.3. Length of the meeting

Too long
Too short
Just right

4.2.4. In thinking about the meetings, you attended in general, what did you think of content and discussion?

too much information
too little information
just right

Comments:
__________________________________________________________________________________________________________________________________________________________________________________________________________________________________________________________________________________________________________________________

4.3. How useful did you find the ESC weekly MDT meetings when you were making your decision about providing personalised patient care and support?

Unhelpful
Fair
Good
Excellent

Comments:
____________________________________________________________________________________________________________________________________________________________________________________________________________________________________________________________________________________________________________________________

5. In thinking about PhotoVoice and the discussions based on reports generated from this exercise, how useful did you find the PhotoVoice reports when you were making your decision about providing personalised patient care and support?

Unhelpful
Fair
Good
Excellent

5.1. To what extent did PhotoVoice help, if at all, clarify understanding the potential strengths and challenges within the older person’s environment?

Unhelpful
Fair
Good
Excellent

5.2. PhotoVoice was intended to provide a deeper exploration and appreciation for the patient’s priorities and response to their treatment decisions. How helpful do you think PhotoVoice was in achieving this intent?

Unhelpful
Fair
Good
Excellent

6. What did you like about PhotoVoice?

____________________________________________________________________________________________________________________________________________________________________________________________________________________________________________________________________________________________________________________________

7. What did you dislike about PhotoVoice?

____________________________________________________________________________________________________________________________________________________________________________________________________________________________________________________________________________________________________________________________

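### Clinician survey item 4.2.2 asks about meeting frequency but offers answers about length, and the PhotoVoice items (5 to 5.2) give no way to say that no report was seen

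*Protocol article*

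**What the plan says.** Appendix A of the protocol article prints the clinician survey. Under the request to rate the multidisciplinary team (MDT) meetings, one item is "4.2.2. Frequency of the meeting" and the next is "4.2.3. Length of the meeting". Both carry the same three answers: *Too long*, *Too short*, *Just right*. No comment line is shown under the frequency item, whereas items 4.2.1, 4.2.4 and 4.3 each have one.

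Three closed items then ask about PhotoVoice, each answered *Unhelpful*, *Fair*, *Good* or *Excellent*:

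- Item 5: "how useful did you find the PhotoVoice reports when you were making your decision about providing personalised patient care and support".
- Item 5.1: "To what extent did PhotoVoice help, if at all, clarify understanding the potential strengths and challenges within the older person’s environment".
- Item 5.2 states the aim of PhotoVoice and then asks: "How helpful do you think PhotoVoice was in achieving this intent".

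None of the three has an answer for a clinician who saw no report. On who is surveyed, Section 3.6 (Recruitment) says "All members of the MDT will receive a study briefing and invitation to participate during their weekly team meeting", with no condition about having seen a report. The only exposure question is item 4.1: "How many meetings did you attend Between February and May 2021", with a note that the dates may be adjusted.

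**The concern.** There are two separate faults in the instrument.

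First, the answers to item 4.2.2 do not fit its question. How often a meeting is held and how long it lasts are different things. A respondent who is dissatisfied with the frequency must pick a duration word, skip the item, or answer the next question twice.

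Second, items 5 to 5.2 assume that every respondent has seen PhotoVoice material. A clinician who has not must leave the items blank or guess, and the data will not show which answers were guesses.

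The second fault matters more. The primary research question, at the end of Section 1, includes the acceptability and utility of PhotoVoice. Items 5 to 5.2 are the only closed questions on PhotoVoice in the surveys shown: the patient survey in Appendix C is about communication with the cancer doctor and does not mention PhotoVoice. Sections 4 and 5 say that the findings will guide a larger trial.

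**Working it through.** The plan states no figure on this point, so the check compares each question with its answers and then follows who can have seen a report.

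**Item 4.2.2**

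| Opinion on frequency | Matching answer offered |
|---|---|
| Meetings held too often | None |
| Meetings not held often enough | None |
| Frequency is right | *Just right* |

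One of three possible opinions can be recorded. *Too long* might mean that the meetings last too long or that the interval between them is too long. *Too short* is ambiguous in the same way. On the second reading, *Too long* would mean too infrequent, so even the direction of the complaint is lost. The answers equal those of item 4.2.3, which suggests that they were copied from one item to the other.

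**Items 5, 5.1 and 5.2**

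1. Who answers: all MDT members are invited (Section 3.6). Item 1.1 lists disciplines as broad as non-clinical supportive services.
2. Who generates a report: allocation is 1:1 (Section 3.3), and only the intervention arm supplies photographs (Section 3.4). The case report for the MDT meeting is built from those photographs and the interview about them (Section 3.7). Control patients generate none.
3. What exposure is recorded: meetings attended (item 4.1). The weekly meeting is part of usual care (Section 3.5), so attending one does not imply that a PhotoVoice report was discussed there.
4. What can be inferred from item 4.1:

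| Meetings attended | Was a report seen? |
|---|---|
| None | Probably not, for the period asked about |
| One or more | Cannot be told |

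**Effect on the result**

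Among those who give a rating, let *u* be the share who saw no report. Let *p* be the proportion of informed raters choosing a given category, and *q* the same proportion among uninformed raters. Then:

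- Observed proportion = (1 − *u*)*p* + *uq*
- Error = observed − *p* = *u*(*q* − *p*)
- As *q* runs from 0 to 1, the error runs from −*up* to +*u*(1 − *p*)

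The documents give neither the size of the MDT nor any basis for *u* or *q*. The error can therefore go either way, and no number can be put on it. With a *not seen* answer that is used as intended and excluded, *u* becomes 0 and the error disappears.

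**The case against.** The case on the other side is substantial, and much of it stands.

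- **Item 4.2.2 is peripheral.** It rates the usual-care MDT meeting, not PhotoVoice. That is right, and the mismatch should not be described as affecting a key PhotoVoice outcome. Nor is the whole item lost: *Just right* still has a clear meaning, and items 3 and 8 let a clinician comment on frequency in free text. Free text does not repair the closed answers.
- **Attendance is recorded.** A clinician who attended no meetings can be identified from item 4.1. That helps for this group only. For everyone else, attendance is a poor stand-in for having seen a report.
- **The scale.** A reader might infer that one clearly negative option out of four pushes the ratings upward, and point to an even spread placing 2/4 = 50% in the top two categories against 2/5 = 40% on a balanced five-point scale. That gap comes from the number of categories: a balanced four-point scale also gives 2/4 = 50%. The protocol sets no success threshold on these items and does not say that categories will be pooled. Leaving out a neutral midpoint is a common forced-choice design and a matter of preference.
- **The lead-in to item 5.2.** A reader might take "PhotoVoice was intended to provide a deeper exploration and appreciation for the" as leading. But the question asks whether an intent was achieved, so the intent has to be stated. Without that sentence the question refers to nothing. Item 5.1 allows for no help at all, and items 6 and 7 ask about likes and dislikes in parallel.

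**Conclusion.** Two faults hold. Item 4.2.2 is wrong as printed: two of three possible opinions on frequency have no answer, and any response other than *Just right* cannot be interpreted. Items 5 to 5.2 cannot separate informed from uninformed ratings, so the denominator for clinician-rated usefulness of PhotoVoice is not defined by exposure.

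A reader might go further and conclude that the ratings are biased in favour of PhotoVoice. The documents do not support that. The error has unknown size and sign, and open items allow criticism.

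The conclusion assumes that Appendix A as printed is the instrument as issued, and that at least some MDT members saw no report. The second is plausible from Sections 3.4 to 3.7 but not stated. No sample size, power or error rate is affected.

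**What to change.** - **Item 4.2.2:** change the answers to *Too often / Not often enough / Just right*.
- **Items 5, 5.1 and 5.2:** add *I did not see a PhotoVoice report*. Exclude those answers from the denominator and report their number separately.

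This is an edit to the survey text, with no extra visits or staff. The small downside is a smaller denominator for the PhotoVoice ratings.

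The documents do not show whether the survey has gone out; recruitment was dated February 2021 to January 2022. If surveys have already been returned, treat off-centre answers to 4.2.2 as uninterpretable. For items 5 to 5.2, report the full distribution over the four categories together with non-response, and state that exposure to reports was not recorded.
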